### Plans for Storage of Vaccine

University Hospital of Reunion Island will be in charge of purchasing the vaccine doses and providing them, via the central pharmacy, to the ASETIS health bus at the intervention college. There will be no change in product packaging, which was identical to the packaging at the time of purchase: 0.5 mL glass prefilled syringes with needles. Labeling (in accordance with current regulations and good clinical practice) referring to use in clinical research will be affixed to the boxes of vaccines intended for the study. The products will be brought by a staff member of the ASETIS association on the days of school vaccination.

The products will be transported, respecting conditions of conservation of the vaccine (kept between 2 °C and 8 °C and protected from light). Expiration date will be checked before any injection. Accounting and traceability of the doses given will be documented by the doctors administrating the vaccination. The health bus has the capacity to store the vaccine doses in the appropriate conditions in a refrigerator.

The products will be stored at the central pharmacy in University Hospital of Reunion Island and in the health bus on vaccination days. The unused doses during the first school vaccination campaign (first dose) will be returned to the hospital central pharmacy to be used during the following campaigns. At the end of the vaccination campaigns, the unused or expired doses will be destroyed according to the regulations in force.

### Statistical Analyses

#### Sample Size

To our knowledge, there are no recent studies that have evaluated the impact of school-based vaccination on HPV vaccination coverage rates. An experimental catch-up vaccination program (diphtheria, tetanus, poliomyelitis, pertussis, measles, mumps, rubella, meningococcus C, hepatitis B, and HPV) in schools in the Vosges (Eastern France) [18] showed a participation rate ranging from 42.9% in the first year to 29% in the second year.

The calculation of the study size is based on the expected proportion of vaccination among girls, as this is the main objective of this study and we have no data for vaccination among boys at this time. Statistical assumptions were as follow:

Proportion of schoolgirls who have had a complete HPV vaccination schedule at the end of school year of 6% in the control group for all students (compared to the 8.1% expected at age 16 years [12])Proportion of schoolgirls with a complete HPV vaccination schedule at the end of the school year of 20% in the intervention group

Thus, 87 girls in each group would need to be included to demonstrate this 14% difference at *α*=.05 and power (1−β=0.80). Assuming 15% nonanalyzable data (lost to follow-up, nonresponse), a total of 103 female students per group would need to be included. As there are roughly as many girls as boys in each class, we would need to include 206 students per group. In order to have an equal representation of each age group, the sampling will be stratified in the grades: 6th, 7th, 8th, and 9th grade. Thus, 52 students per grade and per group should be included.

If we consider that the classes contain an average of 22 students each, a minimum of 3 classes per grade should be randomly selected in each of the 2 middle schools to ensure the minimum necessary recruitment. Thus, randomly selecting 3 classes per grade in each of the 2 middle schools will make it possible to include approximately 132 female students per group and thus to ensure the minimum necessary recruitment. A total of 528 students are expected to be recruited (264 girls [132 per group] and 264 boys [132 per group]). The calculation of the number of subjects required was performed with PASS (version 15, NCSS) software.

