The analysis of barriers to vaccination will describe the causes of nonvaccination reported for students who did not initiate the vaccination schedule. Analyses will be performed for girls and boys separately. We will also compare sociodemographic data, medical history, and health care utilization data between students who initiated HPV vaccination at the end of the school year and those who did not in the intervention group. Bivariate comparisons of percentages will be performed by the chi-square test or Fisher exact test depending on validity conditions. For continuous variables, comparisons will be made using the Student *t* test or the Mann-Whitney *U* test, depending on the conditions of validity. A multivariate analysis by logistic regression will be carried out in order to take into account confounding phenomena: the variable to be explained will be the fact of having initiated vaccination at the end of the school year, and the explanatory variables entered in the model will be the variables for which the significance threshold in bivariate analysis will be ≤.20.

To be determined in the intervention group: among students who initiated HPV vaccination at the end of school year, the proportion of students who used the health bus to initiate this vaccination. Among students who completed the full vaccination schedule at the end of school year, we will determine the proportion who completed all injections on the health bus.

In the intervention group, the proportion of students who used the health bus for sexual health information will be evaluated. In the intervention group, positive and negative points reported by students, their parents, and school staff about this program will be described. Proportion of students up to date for each type of vaccine (according to current vaccination calendar) at the end of school year, in the entire study population as well as in each of the 2 groups (intervention and control), and comparison of these proportions between the 2 groups by the chi-square test or Fisher exact test will be determined, according to validity conditions.

Analyses comparing control group to intervention group will all be performed on an intention-to-treat basis. All hypotheses will be tested with bilateral tests and *α*=.05 and confidence interval calculated at 95%. Analyses will be performed using SAS (version 9.4, SAS Institute Inc) software.

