### Strengths and Limitations

This protocol is submitted more than a year after recruitment began, since sanitary COVID-19 condition was in constant change and evolution and it was difficult to know whether we could continue the process of the trial. Amendments were made and submitted to the ethics committee, facing prohibition of meetings with more than 6 people. This protocol is the result of our constant adaptation to these different obstacles.

Having different exclusion criteria for participants in the intervention and control arms m ay introduce a selection bias by design. However, we wanted to include as many children as possible in the control group to have a representative sample of the population, and the groups may still be comparable. The sample size calculation has not taken into account correlation between participants in the same cluster. As such, the sample size is likely to be too small. However, one limit is the price of the vaccine, which limited our ability to include more students, with regard to the funds allocated.

On Reunion Island, specificities regarding economic and societal development are as follows: high rate of universal health insurance coverage where the high cost of HPV vaccine may be a barrier, mixed culture with religious faith incompatible with premarital sex and racist biopolitical mistrust of the West from which the vaccine comes from, and the particular weight of the antivaccine leagues which casted a negative halo around the subject [25]. Thus we expect a strong veto from parents.

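### The stated 80% power at α=.05 from 87 (103) girls per group assumes independent girls in a trial that draws whole classes; the two figures do not hold together at the higher plausible class correlations

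*Protocol article*

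**What the plan says.** The Sample Size section assumes a "complete HPV vaccination schedule at the end of school year of 6% in the control group" and a "complete HPV vaccination schedule at the end of the school year of 20% in the intervention group", and concludes that "87 girls in each group would need to be included to demonstrate this 14% difference at *α*=.05 and power (1−β=0.80"). It then adds a loss allowance: "Assuming 15% nonanalyzable data (lost to follow-up, nonresponse), a total of 103 female students per group would need to be included". Three classes per grade are drawn in each school. The section expects this to yield about 132 girls per group and says twice that it secures the minimum recruitment needed.

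Study Setting calls the design a cluster trial, with one designated school per arm and 12 classes drawn in each. Statistical Methods for Primary and Secondary Outcomes plans a chi-square or Fisher exact test on individual girls, and states "All hypotheses will be tested with bilateral tests". Strengths and Limitations concedes that the calculation ignored correlation within clusters and that the sample is probably too small, and cites vaccine cost. The same section says "Thus we expect a strong veto from parents".

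**The concern.** The sample size and the design do not match. Girls in one class share a teacher, an information session, a peer group and the same access to the health bus, so their vaccination status is likely to be correlated. A calculation for two independent proportions then overstates the information in the sample.

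The article admits this in its limitations but gives no size for it, and the Sample Size section still presents the draw as sufficient. A reader is told in one place that the minimum is secured and in another that the sample is probably too small.

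Two errors are possible, depending on the analysis. If the analysis respects the classes, power is below the stated figure, and a null result would be over-read. If it does not, as planned, the test rejects too often under the null, and a positive result would be over-read. The second matters here because the stated aim is to extend the programme to all middle schools on the island.

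The 15% loss allowance also looked low, given opt-in consent in the intervention school and the refusal that the article expects.

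**Working it through.** **Inputs from the article.** p₁ = 0.06, p₂ = 0.20, difference 0.14, two-sided α = 0.05, power 0.80, loss 15%, 12 classes per school. Girls per group: 132 (Sample Size), about 128 (half of the 256 students in Sequence Generation), or about 122 (half of the 245 students reported as selected in Results). Half girls is the article's own assumption.

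**Assumption.** The article gives no ICC, so class ICC is set at 0.02, 0.05 and 0.10.

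**1. Reproduce the plan's figures.** With unpooled variance:

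n = (1.960 + 0.842)² × (0.06×0.94 + 0.20×0.80) / 0.14² = 86.7, so 87.

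87 / 0.85 = 102.4, so 103.

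Both match. (The pooled-variance version gives 89.4, so 90.) The arithmetic is right for independent girls.

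**2. Analysable girls under the plan.** 122 × 0.85 ≈ 104 and 132 × 0.85 ≈ 112. Under independence these give about 87% and 89% power.

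**3. Power of a test that respects classes.** Design effect DE = 1 + (m − 1) × ICC, with m = n/12. Power = Φ(0.14 / √[(0.0564 + 0.1600) × DE / n] − 1.960).

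| Analysable girls per group | m | ICC 0.02: DE, power | ICC 0.05: DE, power | ICC 0.10: DE, power |
|---|---|---|---|---|
| 87 | 7.25 | 1.12, 75% | 1.31, 69% | 1.62, 60% |
| 104 | 8.67 | 1.15, 82% | 1.38, 74% | 1.77, 64% |
| 112 | 9.33 | 1.17, 84% | 1.42, 76% | 1.83, 65% |

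The pooled formula gives values 1 to 2 points lower.

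**4. Class ICC at which 80% is lost.** Setting n/DE = 87:
- n = 104: DE = 104/87 = 1.195, so ICC = 0.195/7.67 ≈ 0.025.
- n = 112: DE = 112/87 = 1.287, so ICC = 0.287/8.33 ≈ 0.034.

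**5. The planned unadjusted chi-square.** Simulated with beta-binomial classes, 12 per arm, 100,000 runs per cell. Power is at 6% versus 20%; type I error is at 6% in both arms.

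| Girls per group | ICC 0.02: power, type I | ICC 0.05: power, type I | ICC 0.10: power, type I |
|---|---|---|---|
| 87 | 80%, 6% | 78%, 8% | 76%, 11% |
| 104 | 86%, 6% | 84%, 9% | 81%, 14% |
| 112 | 89%, 7% | 86%, 10% | 83%, 14% |

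The approximation 2[1 − Φ(1.960/√DE)] agrees: at n = 104 it gives 6.8, 9.6 and 14.0%.

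**6. Loss.** With no clustering, 87 analysable girls remain until 1 − 87/132 = 34% are lost, or about 29% if 122.5 girls were selected.

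**7. Between schools.** None of the above includes school-level variance. With one school per arm it cannot be separated from the programme effect, and more girls in the same schools would not reduce it. For scale, at 112 girls per group an assumed school ICC of 0.005 to 0.01 would put the unadjusted test's type I error at about 12 to 18%.

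**The case against.** **The plan does not stop at 103.** It expects about 122–132 girls per group. After 15% loss that gives 87–89% power under independence, and 80% survives up to a class ICC of about 0.025–0.034. This stands: a reader might infer that the trial as drawn certainly falls below 80%, but that depends on an ICC the article does not give. The article never presents the surplus as an allowance for clustering, however, and 132 is optimistic: it assumes 22 students per class, while one class in three comes from the adapted-education sections, which are capped at 16.

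**The planned test keeps its power.** With 104–112 girls, the unadjusted chi-square has about 81–89% power across the ICC range. This also stands, so the power figures in step 3 must not be read as those of the planned test. The unadjusted test gets there by exceeding α=.05, so the stated pair is still not met.

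**The 15% is not contradicted.** A reader might set it against the cited catch-up programme, which "showed a participation rate ranging from 42.9% in the first year to 29% in the second year". That figure is uptake of a vaccination programme, not availability of data. Eligibility Criteria and the June data collection both let students who are not vaccinated in the bus contribute data. In the COVID-19 route, control data are taken unless parents object. The expected parental veto carries no number, and refusal before inclusion bears on the 132 more than on loss afterwards. What remains is that the 15% has no source and sits uneasily with consent forms to be signed by both parents.

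**The limitation is disclosed.** It is, with a cost reason. That explains why more students were not enrolled; it does not explain leaving the power claim unchanged.

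**Conclusion.** The point holds in limited form. The figures 87 and 103 are correct arithmetic for a design the trial does not have. Over an assumed class ICC of 0.02 to 0.10, a valid test has about 75 to 60% power at the stated 87 girls and 82 to 64% at 104. The girls actually drawn support 80% only up to a class ICC of about 0.025–0.034. The planned unadjusted test holds about 81–89% power at 104–112 girls, but with type I error of about 6–14%. So α=.05 and 80% power are not delivered together at the higher ICCs.

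These results rest on the assumed ICCs, equal class sizes, the planned 6% and 20%, and 15% loss; they exclude between-school variance. The 15% should be called unsupported, not wrong. Because the article already discloses the ignored correlation, what needs correcting is the uncorrected claim and its missing size.

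**What to change.** In Sample Size:
- Keep 87 and 103 as the calculation for independent girls, and say so.
- Replace the 80% claim with a short table of power, or detectable difference, at a valid α=.05 for the sample drawn: 12 classes per school, about 122–132 girls per school, class ICC 0.02–0.10, and a range of analysable fractions. Label the ICCs and fractions as assumptions.
- Give the type I error of the unadjusted chi-square beside each row.
- State that the table excludes between-school variance, which one school per arm cannot estimate.
- Remove the statements that the draw secures the minimum recruitment needed, and cross-refer to the clustering caveat in Strengths and Limitations.
- Give a source for the 15%, or mark it as an assumption.

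The cost is one table and some restated text. Vaccination recruitment is already complete, and no further students are asked for. The downside is a less favourable stated power.

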#### Sequence Generation

In priority education schools, there are classes called Sections d’enseignement general et professionnel adapté (SEGPA; adapted general and vocational education sections): these classes, from 6th to 9th grade, are integrated into the middle school. They welcome young people who have significant school difficulties that cannot be resolved by academic assistance and support. There is only a small group of students (16 maximum) in each class in order to individualize each student's progress. SEGPA classes should enable students to access at least a professional qualification.

In the Paul Hermann Middle School, there are 9 classes in each grade, including 2 classes of SEGPA per grade. In the Plateau Goyave Middle School, there are 9 classes in 6th grade and 9th grade and 10 classes in 7th and 8th grade, including 2-3 classes of SEGPA per grade. In each of the selected middle schools, 12 classes will be randomly selected in order to have a balanced number of students in each arm.

In order to have an equal representation of each age group, the sampling will be stratified on the grade (6th, 7th, 8th, and 9th grade), and in order to take into account the specificities of SEGPA classes, we decided to stratify on SEGPA classes as well. As the main point in this comparative trial was similarity of the 2 groups compared, we decided to randomly select 1 SEGPA class per grade and 2 non-SEGPA classes per grade. Thus we will include in this trial 256 students from Paul Hermann Middle School (intervention group) and 255 students from Plateau Goyave Middle School (control group).

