#### Statistical Methods for Primary and Secondary Outcomes

The aim of this study is to compare clinical outcomes between classes from a middle school sensitized to HPV vaccination through a combined health promotion program (intervention group) and a middle school without any specific action (control group). The null hypothesis is that there is no difference in the groups. For descriptive analyses, qualitative variables will be described in terms of frequencies and percentages with their 95% confidence intervals; quantitative variables will be expressed in terms of means, standard deviations, and 95% confidence intervals or in terms of medians and IQRs (25th and 75th percentiles).

Comparability of groups at inclusion will be checked: bivariate comparisons of categorical variables will be performed by the chi-square test or Fisher exact test, depending on the conditions of application. Bivariate comparisons of means will be performed by the Student *t* test or Mann-Whitney *U* test, depending on the conditions of application. For the analysis of the primary outcome: the proportion of schoolgirls who will have completed the full HPV vaccination regimen at the end of the school year will be compared between the 2 groups (intervention and control) by the chi-square test or Fisher exact test, according to validity conditions.

Concerning secondary outcomes analysis: the proportion of schoolgirls who initiated HPV vaccination (1 dose) by the end of school year will be compared between the 2 groups (intervention and control) by the chi-square test or Fisher exact test according to validity conditions. The proportion of boys who will have completed the full vaccination schedule at the end of school year will be compared between the 2 groups (intervention and control) by the chi-square test or Fisher exact test, according to validity conditions. The proportion of boys who will have initiated the vaccination scheme at the end of the school year will be compared between the 2 groups (intervention and control) by the chi-square test or Fisher exact test, depending on the conditions of validity.

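### Classes are drawn by grade and SEGPA, but the between-group tests are fixed as crude comparisons that ignore both; adjusting for them is a small, low-cost improvement

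*Protocol article*

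**What the plan says.** **The draw (Protocol article, Sequence Generation).** Sampling is stratified by grade and by SEGPA status. For the sake of similar groups, "we decided to randomly select 1 SEGPA class per grade and 2 non-SEGPA classes per grade", in each school. In the intervention school "there are 9 classes in each grade, including 2 classes of SEGPA per grade". The control school has 9 classes in 6th and 9th grade and 10 in 7th and 8th, of which 2 to 3 per grade are SEGPA; the split by grade is not given. A SEGPA class holds at most 16 pupils.

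**The analysis (Statistical Methods for Primary and Secondary Outcomes).** Completion of the schedule among girls is compared between arms "by the chi-square test or Fisher exact test, according to validity conditions". Initiation among girls, both boys' outcomes and the other vaccines get the same type of test. The only multivariable model concerns predictors of initiation within the intervention group.

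**Who enters the analysis.** In the intervention school, health-record data are collected for children whose parents signed a consent form. In the control school, under the COVID-19 procedure, data are collected unless an objection form comes back, although the same section also mentions signed consent. The Eligibility Criteria apply exclusions to the intervention group only, and Strengths and Limitations concedes that this may introduce selection bias.

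**The concern.** The plan treats grade and SEGPA as important enough to structure the draw, then drops both from the comparison. Grade matters by the article's own account: Sample Size assumes 6% completion across all grades against 8.1% at age 16, and the number of doses that makes a complete schedule changes at age 15.

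A crude two-by-two table relies on the drawn mix surviving into the analysed set. With opt-in in one arm, something close to opt-out in the other, and one-sided exclusions, participation may vary by grade and SEGPA differently in the two arms. One exclusion, HPV vaccination already initiated, is likely to bear more on older girls, although the wording leaves unclear whether it removes them from the data or only from the health bus. At stake is a modest, avoidable imbalance in the primary contrast and a small loss of precision.

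**Working it through.** **1. The plan's own figure.** Inputs from Sample Size: completion "at the end of school year of 6% in the control group for all students" and "at the end of the school year of 20% in the intervention group", α = 0.05, power 0.80, and "All hypotheses will be tested with bilateral tests" from the statistical methods. With unpooled variance:

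n = (1.960 + 0.842)² × (0.06×0.94 + 0.20×0.80) / 0.14² = 7.849 × 0.2164 / 0.0196 = 86.7, so 87 per group. Then 87/0.85 = 102.4, so 103.

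Both figures reproduce. They contain no strata, and this point does not alter them.

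**2. Selection probabilities** (classes drawn / classes available).

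| Grade type | SEGPA | Other |
|---|---|---|
| Intervention, every grade | 1/2 = 0.50 | 2/7 = 0.286 |
| Control, 9 classes, 2 SEGPA | 0.50 | 2/7 = 0.286 |
| Control, 9 classes, 3 SEGPA | 0.33 | 2/6 = 0.33 |
| Control, 10 classes, 2 SEGPA | 0.50 | 2/8 = 0.25 |
| Control, 10 classes, 3 SEGPA | 0.33 | 2/7 = 0.286 |

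**3. Resulting mix** (245 of 780 and 259 of 834 pupils, from Results; 16 per SEGPA class is an assumption at the stated maximum).

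- Intervention: sample 4×16/245 = 26%; school 8×16/780 = 16%.
- Control: sample 64/259 = 25%; school 8 to 12 classes × 16 / 834 = 15–23%.

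The two samples match each other (26% and 25%). Neither need match its school.

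**4. If the analysed mix drifts apart.** Let w be the stratum share in an arm and p the intervention coverage in the stratum. Relative to standardising on the control mix, the crude difference is off by Σ(w_int − w_con) × p. The documents give no stratum coverage or participation, so these are illustrations only:

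- SEGPA coverage 10.9% against 21.8% elsewhere, SEGPA share differing by 10 points: 0.10 × 10.9 = 1.1 points.
- Coverage 5% in 6th grade and 35% in 9th, with 10 points of share moved between those grades: 0.10 × 30 = 3.0 points.

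The planned difference is 14 points.

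**5. Precision.** The share of variance removed by stratifying is the between-stratum variance of p, summed over arms, divided by 0.2164. All coverages by grade are assumed.

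- *Mild gradient* (15, 18, 22, 25% against 3, 5, 7, 9%): (0.00145 + 0.00050)/0.2164 = 0.9%; SE ratio √(1 − 0.009) = 0.995.
- *Steep gradient* (5, 15, 25, 35% against 0, 4, 8, 12%): (0.0125 + 0.0020)/0.2164 = 6.7%; SE ratio 0.966.
- Adding SEGPA at half the grade average (25% of the sample): 2.7% and 8.9%; SE ratios 0.987 and 0.954.

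The standard error therefore falls by about 0.5–5%.

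**6. Sample percentage against school coverage.** Take true school coverage of 20% and 6% and a SEGPA sample share of 25%. If SEGPA coverage is half that of the others, unweighted figures are 19.1% (intervention) and 5.7–5.9% (control). With SEGPA coverage from 0 to 2 times the others, they span 17.9–21.5% and 5.3–6.5%.

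**The case against.** The strongest reply is that the draw already does the work. Both arms receive one SEGPA and two other classes in every grade, so the crude contrast is not materially confounded by these factors at selection. That stands for the classes drawn. It does not guarantee the same mix among the girls analysed.

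A second reply is that adjusted analyses belong in a statistical analysis plan. But the article is not silent: it names the test for the primary outcome and for every between-group proportion.

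Three stronger readings are tempting and not supported:

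- *The percentages misstate school coverage and must be weighted.* The article sets a comparison between sampled classes and says the draw was chosen for similarity of the groups. Only looser wording in the abstract and discussion speaks of coverage in the schools. Weighting would move SEGPA to 16% in one arm and 15–23% in the other, which could undo the matched mix. It would raise variance by about 0–6%, roughly what stratifying gains. The control-school weights cannot be derived from 2 to 3 SEGPA classes per grade.
- *SEGPA pupils are over-sampled throughout.* A 9-class control grade with three SEGPA classes has equal probabilities.
- *Substantial precision is thrown away, or false positives rise.* The gain is small, and ignoring strata tends to make the crude test slightly conservative.

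**Conclusion.** The point holds as a minor improvement. The stated between-group tests ignore the two factors that define the draw, and participation rules that differ by arm mean balance among the analysed girls cannot be taken for granted. The expected precision gain is a standard error about 0.5–5% smaller, resting on assumed coverage by grade and SEGPA. The protection against imbalance cannot be sized from the documents; the illustrations above give 1 to 3 points against a planned 14.

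Adjustment removes only imbalance in grade and SEGPA. It does not correct consent-related selection within strata, differences between the two schools, or class clustering. Clustering is the larger issue. With 108 analysable girls per arm (256/2 × 0.85, rounded down) and 128/12 = 10.7 girls per class, power is 87% ignoring it, and 84%, 71% and 59% at assumed class-level intraclass correlations of 0.01, 0.05 and 0.10.

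**What to change.** - Make the primary comparison a risk difference with 95% confidence interval, stratified by or adjusted for grade and SEGPA (Mantel-Haenszel, or model-based standardisation). Keep the crude table as descriptive, and treat the other between-group proportions in the same way.
- Mantel-Haenszel suits the sparse strata. A SEGPA class of 16, half girls, gives 8 girls and about 0.06 × 8 = 0.5 expected control events. If a model is used, enter grade and SEGPA as main effects.
- Do not promise a full design-based variance. With one SEGPA class per grade per school, between-class variance within those strata cannot be estimated, so class clustering needs its own statement.
- Tabulate analysed girls by grade and SEGPA in each arm, so that any drift from the drawn mix is visible.
- Describe arm percentages as those of the sampled classes, not as whole-school coverage. Use no inverse-probability weights in the comparison.

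The cost is wording. Grade and SEGPA status are known from the class drawn, and no new data are needed. Because the article reports that analyses are under way, the change should be dated and declared as made before or after outcome data by arm were seen.
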